#### Phase II treatment:

For patients with metastatic gastrointestinal tumors (colon, pancreas, stomach, and bile ducts), a total of 30 new patients will be enrolled and divided into two groups: an intervention group and a placebo group, each consisting of 15 patients. The intervention group will receive continuous treatment with the Esperanza extract at the determined maximum tolerated dose (MTD) for three treatment cycles, equivalent to approximately 12 weeks. The placebo group will receive a placebo in addition to standard chemotherapy treatment for their underlying disease. Safety evaluations will be conducted at the end of each treatment cycle, and the efficacy evaluation will be carried out after completion of the three treatment cycles. Table 2 provides a comprehensive list of the activities to be carried out during the patients' intervention.

**Table 2 Tab2:** Activity schedule for phase II clinical trial in gastrointestinal tumors

Schedule of activities					

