### Provisions for post-trial care {30}

All participants will be monitored for a period of 1 month following the completion of their treatment. Additionally, after their final visit, participants will be informed that they have the option to seek clarification or report any new signs or symptoms through telephone or in-person consultations. Furthermore, patients will continue to receive regular clinical follow-up for their underlying disease, adhering to the established schemes and protocols at the Hospital.

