### Outcomes {12}

The primary outcome of this study is to determine the safety, efficacy, and maximum tolerated dose (MTD) of the administration of the Esperanza extract in patients with metastatic gastrointestinal tumors as well as in patients with acute leukemias. Additionally, the study aims to assess the impact of the Esperanza extract on the quality of life of these patients using the QLQ-C30 scale. The evaluation period will be between 4 and 6 months, and the QLQ-C30 version 3 scale will be employed as the standardized method for assessing the patients' quality of life outcomes.

The secondary outcomes of this study are as follows:To determine the effect of treatment with the Esperanza extract in combination with chemotherapy on the clinical and pathological response. This evaluation will be conducted between 1 and 3 months using the Recist 1.1 (Response Evaluation Criteria In Solid Tumors) scale as the standardized evaluation method and with flow cytometry and myelogram in acute leukemias.To assess the impact of treatment with the Esperanza extract in combination with chemotherapy on the number and size of metastases. This assessment will also be carried out between 1 and 6 months, utilizing the Recist 1.1 for gastrointestinal tumors and cytometry and myelogram for acute leukemias.To determine progression-free survival and overall survival. The evaluation period for progression-free survival will be 3 months, and the Log Rank test will be used as the evaluation method. Progression-free survival will be measured from randomization to the occurrence of disease progression, local or distant recurrence, development of a second primary malignancy, or death from any cause, whichever occurs first. Patients who do not meet the evaluation time point will be censored and followed up until the end of treatment for survival curve preparation.

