### Participant timeline {13}

#### Sample size {14}

For phase I, a sample size of 6 patients was determined for gastric tumors and acute leukemias. In case of presentation of any adverse event in the first in these patients, the dose will be decreased for the second cycle; in case of an adequate safety profile, the dose will be doubled for the second cycle.

The sample sizes for phase II were determined for both gastrointestinal tumors and hematologic tumors. For gastrointestinal tumors, a sample size of 30 patients was calculated, with 15 patients per group, considering a mean difference of at least 6 points in quality of life, a standard deviation of 5 and 6 points for each group, an alpha error of 0.05, and a beta error of 0.20. Additionally, a 10% allowance was added for possible study losses. For hematologic tumors, the sample size calculation was based on response criteria such as improvement, remission rate, and hematologic recovery. The ANOVA test was used, an alpha error of 0.05, a beta error of 0.20, and an effect size of 0.4. The resulting sample size was 28.

It should be noted that these sample sizes will be reassessed at the end of phase I for both gastric tumors and acute leukemia. The recalculated sample size for phase I/II is 36 for gastrointestinal tumors and 46 for hematologic tumors.

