## Statistical methods

### Statistical methods for primary and secondary outcomes {20a}

A descriptive analysis of the study database will be conducted, including measures of central tendency (such as mean, median, and mode) and dispersion (such as standard deviation and range) for quantitative variables, as well as frequencies and counts for categorical/ordinal variables. In cases where data is missing, an active search will be performed in the electronic clinical record system (SAHI®) of the Hospital, clinical laboratory database (LabCore®), and directly from the patient to retrieve the missing information.

No imputation method is expected to be used, and only patients with complete information will be included in the analysis for each specific objective. For exploratory analyses, the normality of each quantitative variable will be assessed to determine the appropriate use of statistical tests. Depending on the distribution of the data, parametric tests such as the Student's t-test and ANOVA may be used for comparisons between groups, while non-parametric tests such as the Kruskal–Wallis and Mann–Whitney test may be used for non-normally distributed data. The Logrank test will be utilized for survival outcomes associated with that objective.

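### Phase II gastrointestinal PFS is planned as a survival curve with a log-rank test, but a single post-baseline scan cannot date progression; analysed at scan dates, the curve ends too low

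*Protocol article*

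**What the plan says.** Outcomes {12} lists PFS as a secondary outcome and defines it as a time to event: "Progression-free survival will be measured from randomization to the occurrence of disease progression, local or distant recurrence", a second primary malignancy or death. The same paragraph fixes the horizon and the test: "The evaluation period for progression-free survival will be 3 months, and the Log Rank test will be used as the evaluation method". Patients who do not reach the evaluation time point "will be censored and followed up until the end of treatment for survival curve preparation". Statistical methods {20a} repeats the test: "The Logrank test will be utilized for survival outcomes associated with that objective".

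Table 2, the gastrointestinal phase II schedule, marks RECIST at the initial visit (Week 2) and at close-out (Week 12-14) only. The PFS row carries the same two marks. Cycles 2 and 3 are blank in both rows, while QLQ-C30 is marked at both cycles and several laboratory measures at cycle 3, so the blanks look deliberate. The text under Phase II treatment agrees: treatment runs "for three treatment cycles, equivalent to approximately 12 weeks", and "the efficacy evaluation will be carried out after completion of the three treatment cycles". Provisions for post-trial care {30} adds "All participants will be monitored for a period of 1 month following the completion of their treatment" but names no scan. Sample size {14} gives the arm size: "a sample size of 30 patients was calculated, with 15 patients per group".

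**The concern.** The endpoint, schedule, test, curve and end of follow-up are all stated in the article, and they do not fit together. With one scan after baseline, a patient found to have progressed did so at some unknown point in the preceding 10 to 12 weeks. An ordinary Kaplan-Meier analysis puts that event on the scan date and censors an event-free patient on his or her own scan date. Inside the close-out window, the order of events is then the order of appointments. A non-progressor scanned early leaves the risk set; a progressor scanned days later is counted against a smaller denominator.

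PFS is a named efficacy outcome of the trial's only randomised comparison, and the Discussion looks ahead to phase III. A 3-month PFS or median read from such a curve would partly reflect visit timing and could misinform that planning.

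**Working it through.** **Inputs from the article.** 15 patients per arm; one post-baseline scan in Week 12-14, which is 10 to 12 weeks after the Week 2 visit and 11 to 13 weeks after Week 1; follow-up for the curve ends with treatment. The article gives no PFS rate, event count or power. Its 15 per arm comes from quality of life and reproduces: n = (1.96 + 0.84)² × (5² + 6²) / 6² ≈ 13.3 per arm, and 13.3 / 0.9 ≈ 14.8, rounded to 15. That figure is not in question and serves only as the arm size below.

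**Assumptions.** True PFS at the scan of 70%, 50% and 30%; scan days uniform over 14 days; the share of progressions or deaths dated before the scan varied from none to half.

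**Check by formula.** Let p be the probability of progression by the scan, with all scan dates distinct and nothing dated earlier. When k patients remain at risk, the next one scanned multiplies the curve by 1 − 1/k with probability p, and by 1 otherwise: on average 1 − p/k. The expected final value is

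E[KM] = ∏ (1 − p/k), k = 1 to 15.

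The k = 1 factor alone equals the true PFS, 1 − p. The other 14 factors are all below 1, so the result must be too low. For p = 0.3, 0.5 and 0.7 the product is 0.34, 0.144 and 0.05, against true values of 0.70, 0.50 and 0.30.

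**Simulation, 6,000 arms of 15, ties allowed.** Mean Kaplan-Meier value at the end of the window:

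| True PFS | No event dated before the scan | Half dated before the scan | None dated earlier, all scans within 5 days |
|---|---|---|---|
| 70% | 39% | 50% | 47% |
| 50% | 18% | 28% | 25% |
| 30% | 7% | 12% | 11% |

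Runs with different seeds differ by about one point. At true PFS of 50% with nothing dated earlier, the curve ends at exactly zero in about 37% of arms.

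**Before the window.** The error has the opposite sign. With exponential progression and true 3-month PFS of 60%, true 8-week PFS is 0.60^(56/91) = 0.73; the curve reads 1.00 if no event is seen between scans. With true 3-month PFS of 70% and half of events dated early, it reads about 0.90 against 0.70^(56/91) = 0.80.

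**Dependence on the dating rule.** With true 3-month PFS of 60% and scans on days 70-84, the proportion progression-free at the scan is about 0.65. Kaplan-Meier at actual scan dates gives about 0.30. Giving all scans one nominal date, or keeping event-free patients at risk to the end of the window, gives 0.65. Censoring them at an end of treatment 0 to 7 days before the scan gives 0.13.

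**The test.** With equal scan timing in both arms, the log-rank test on scan dates rejects in about 5% of null trials. For power, assume medians of 84 and 252 days and scans on days 71-84, so that the mean event probabilities are 0.472 and 0.192:

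| Test | Power |
|---|---|
| Log-rank, true event times | about 39% |
| Uncorrected chi-square on progressed yes/no | about 39% |
| Log-rank, one nominal scan time | about 33% |
| Log-rank, actual scan dates | about 25-27% |
| Fisher's exact | about 21-22% |

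**The case against.** The strongest reply is that the downward bias depends on a dating and censoring rule that the article does not state. A 3-month evaluation period can be read as a nominal time point, such rules are often left to an analysis plan that is not shown here, and under a nominal date the understatement disappears. This stands as a limit on certainty: the article permits the bias but does not impose it. It does not remove the point. No nominal-date rule is given, follow-up for the curve stops with treatment, and a nominal date still cannot recover when progression occurred.

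Second, Outcomes {12} places RECIST response between 1 and 3 months, and metastasis count and size between 1 and 6 months, which might imply further scans. Table 2 schedules none, and the Phase II treatment text describes one efficacy evaluation after three cycles.

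Third, assuming that nothing is dated before the scan is a worst case. Eligible patients have metastatic disease and need a life expectancy of only more than 2 months. They attend at cycles 2 and 3 and receive weekly calls, and deaths have exact dates. This is fair, and the half-dated-early column is the better lead. It reduces the bias without removing it.

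A reader might also infer that the log-rank test is invalid. The documents do not support that. Its size holds when scan timing is alike in the two arms. In an extreme case with one arm scanned on days 70-76 and the other on days 78-84, it rejects in about 95% of null trials, but nothing in the double-blind design suggests such a split. Nor does any comparison of proportions gain power: Fisher's exact test has less than the scan-date log-rank test.

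**Conclusion.** The concern holds in a limited form. One post-baseline scan in a two-week window cannot support a time-to-progression curve or a median PFS. If scans are analysed at their actual dates, the curve at the end of the window is too low: about 50%, 28% and 12% for true PFS of 70%, 50% and 30% when half of progressions are dated earlier, and about 39%, 18% and 7% when none are. These sizes rest on assumed PFS rates, a uniform 14-day spread of scans and scan-date analysis. The direction does not depend on the assumed rates, but it does depend on the scan-date rule.

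It would be too strong to say that the plan as written necessarily understates 3-month PFS, or that the log-rank comparison is unsound. PFS is secondary, and the quality-of-life sample size is unaffected. The correction should be made, but the point does not threaten the primary analysis.

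**What to change.** In Outcomes {12} and Statistical methods {20a}, make the gastrointestinal PFS estimate the proportion alive and progression-free at the close-out assessment. Count deaths and earlier clinical progressions as events. Give an exact confidence interval per arm, and compare the arms by an uncorrected chi-square or a similar unconditional test. Do not present Fisher's exact test as a gain in power.

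If a curve and log-rank test are kept, assign every close-out scan one nominal time, with earlier dated events kept at their own dates, or use an interval-censored estimator and test.

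The cost is wording only, with no extra scans or patients. No median PFS would be reported, but this schedule cannot support one in any case. A proportion also needs a stated rule for patients lost before close-out without a known event, whom a survival curve would simply censor.

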### Participant timeline {13}

#### Sample size {14}

For phase I, a sample size of 6 patients was determined for gastric tumors and acute leukemias. In case of presentation of any adverse event in the first in these patients, the dose will be decreased for the second cycle; in case of an adequate safety profile, the dose will be doubled for the second cycle.

The sample sizes for phase II were determined for both gastrointestinal tumors and hematologic tumors. For gastrointestinal tumors, a sample size of 30 patients was calculated, with 15 patients per group, considering a mean difference of at least 6 points in quality of life, a standard deviation of 5 and 6 points for each group, an alpha error of 0.05, and a beta error of 0.20. Additionally, a 10% allowance was added for possible study losses. For hematologic tumors, the sample size calculation was based on response criteria such as improvement, remission rate, and hematologic recovery. The ANOVA test was used, an alpha error of 0.05, a beta error of 0.20, and an effect size of 0.4. The resulting sample size was 28.

It should be noted that these sample sizes will be reassessed at the end of phase I for both gastric tumors and acute leukemia. The recalculated sample size for phase I/II is 36 for gastrointestinal tumors and 46 for hematologic tumors.

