## Assignment of interventions: allocation

### Sequence generation {16a}

During the screening visit, all participants will be assigned a unique subject number in sequential order (e.g., 001, 002, 003, etc.), which will remain consistent throughout the study. The treatment chosen by the attending physician will be administered to all participants, without randomization in phase I.

In phase II, patients with gastrointestinal tumors will undergo randomization using a specially designed application within the eCRF in RedCap®. The randomization will be conducted using a simple non-stratified approach, predetermined, and loaded into the eCRF for the pharmacist, who will be unblinded. Randomization will not be employed for acute leukemias, as the comparison of outcomes will be conducted against a historical group using propensity score matching.

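### Phase II gastrointestinal arm: the normal formula behind 30 patients leaves no room for the 10% loss once a t-test is used, so power at 27 complete cases is about 77%, not 80%

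*Protocol article*

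**What the plan says.** All statements are in the protocol article.

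- **Sample size {14}**, phase II gastrointestinal: "a sample size of 30 patients was calculated, with 15 patients per group". The inputs behind this number are a 6-point difference between means, SDs of 5 and 6 in the two arms, alpha 0.05 and power 0.80. On losses the section says: "Additionally, a 10% allowance was added for possible study losses". Neither the formula nor the sidedness of alpha is given.
- **Phase II treatment**: "a total of 30 new patients will be enrolled and divided into two groups", of 15 each. Thirty is therefore the enrolled number, after any inflation.
- **Statistical methods {20a}**: between-group comparisons may use Student's t-test or ANOVA if the data look normal, and Mann–Whitney or Kruskal–Wallis otherwise.
- **Statistical methods {20a} and the missing-data section {20c}**: no imputation is expected, and each objective is analysed in patients with complete information only.
- **Sequence generation {16a}**: a predetermined list is loaded into the eCRF, made "using a simple non-stratified approach".
- **Sample size {14} and Interim analyses {21b}**: sample sizes will be reassessed after phase I.

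**The concern.** Under a complete-case rule every lost patient comes off the analysed number. A loss allowance works only if the number left after the losses still gives the stated power under the test that will be used. With about 14 patients per arm, the normal formula asks for fewer patients than a t-test does, and here that gap is about the size of the allowance. If so, the stated 80% holds only if nobody is lost.

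This is the trial's only randomised comparison, and quality of life is the main efficacy outcome for this group. The power figure is what a reader would use to judge a result that shows no difference.

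**Working it through.** **Inputs.** Difference 6; SDs 5 and 6; alpha 0.05; power 0.80; 15 per arm enrolled; 10% loss (Sample size {14}). Complete cases only ({20a}, {20c}). Two-sided alpha is an assumption, tested in step 1.

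Common SD = √((25 + 36)/2) = √30.5 = 5.523. Standardised difference = 6/5.523 = 1.086.

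**1. Reproducing the plan's figure (normal formula).**

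n per arm = (z₁₋α/₂ + z₁₋β)² × (5² + 6²)/6² = (1.960 + 0.842)² × 61/36 = 13.30.

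- Loss allowance: 13.30/0.9 = 14.78, or 13.30 × 1.1 = 14.63. Both round up to 15 per arm, 30 in total. The figure reproduces.
- If 13.30 is rounded to 14 before inflating: 14/0.9 = 15.6, so 16 per arm, 32 in total.
- One-sided alpha of 0.05: (1.645 + 0.842)² × 61/36 = 10.48, or 12 to 13 per arm after inflation, 24 to 26 in total. This does not reproduce 30, so two-sided is the reading that fits.
- Normal-formula power at 13.5 per arm is 80.6%, which matches the stated 80%.

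**2. Power of the two-sided t-test (noncentral t, pooled variance).**

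Noncentrality = 6/(5.523 × √(1/n₁ + 1/n₂)), with n₁ + n₂ − 2 degrees of freedom.

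| Evaluable patients | Noncentrality | Critical t | Power |
|---|---|---|---|
| 15 + 15 (no losses) | 2.975 | 2.048 | 81.9% |
| 14 + 14 | 2.874 | 2.056 | 79.0% |
| 13 + 14 (27, a 10% loss) | 2.821 | 2.060 | 77.4% |
| 13 + 13 | 2.770 | 2.064 | 75.7% |

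Fifteen evaluable per arm is thus the smallest equal-arm size that reaches 80%, before any loss. The unequal-variance (Welch) version changes little: 75.6% at 26, and 76.9% to 77.6% at 27 depending on which arm is smaller.

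**3. Sensitivity to allocation, at 27 evaluable.**

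- Arms fixed at 15/15 and three patients lost at random: 77.3%.
- Arm sizes left to chance, averaged over Binomial(27, 0.5): 75.8%.

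**4. Adjusting for baseline QLQ-C30, at 27 evaluable.**

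Residual SD = 5.523 × √(1 − r²), with one further degree of freedom used. This takes 5 and 6 to be SDs of follow-up scores. The correlation r is not in the document and is assumed.

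- r = 0.3: about 81%.
- r = 0.5: about 88%.

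**The case against.** **The number is right by a standard formula.** It is: 30 reproduces with the allowance inside it, and rounding once at the end is ordinary practice. A reader might infer that the 10% was never added, or that the sum is wrong. The document supports neither. What stands is narrower: a large-sample formula was used for a small-sample t-test, and the difference consumes the allowance.

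**The test and the sidedness are not fixed.** This is partly so. The t-test is named as one that may be used, depending on the distribution, in a sentence framed around exploratory analyses, and alpha has no stated side. A one-sided test at 13 per arm would have 85% power, but one-sided testing does not lead to 30. Mann–Whitney would not restore 80%: with the usual efficiency of about 0.955, which itself assumes normal data, power at 27 is about 75%.

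**Arm sizes are fixed at 15.** A reader might infer from the simple allocation that power definitely falls to 76%. The wording may mean no more than unstratified, and two sections state 15 per group. The 76% is therefore conditional on an unrestricted list; the main result does not need it.

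**The size is provisional.** It is to be reassessed after phase I, and that is a natural time to correct the statement, but the promise does not make the present figure right. The recalculated total of 36 for phase I/II equals 30 + 6, the phase I patients, so it appears to add no one to phase II. The phase I schedule as printed (Table 1) lists no QLQ-C30.

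**The gap is trivial.** It is small. Losing one patient per arm leaves 79.0%, and a true difference of 6.2 instead of 6 would bring power at 27 back to 80%. The SDs are planning values with more uncertainty than that, and the Discussion leaves efficacy to phase III. It would go too far to say that a null result will be over-read because power is 77% and not 80%.

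**Conclusion.** The point holds in a limited form. With the plan's own difference, SDs, loss rate and complete-case rule, a two-sided t-test has about 77% power at 27 evaluable patients (75.7% at 26) and about 82% with no losses. The stated 80% after a 10% loss holds only under the normal approximation. The shortfall is about 3 points.

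This rests on two-sided alpha of 0.05, which is not stated but is the only side that reproduces 30, and on the t-test being the test used. The lower average of about 76% applies only if the randomisation list does not force 15/15. This is a minor correction to one stated figure and does not threaten the design.

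**What to change.** Either change is enough, and neither adds patients or visits.

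1. **Restate the power.** In Sample size {14}, say that 30 patients give about 82% power with no losses and about 77% at 27 evaluable patients, for a two-sided t-test at 0.05. Name the test and the sidedness, and say whether the list is balanced to 15/15. The cost is one or two sentences and a slightly less favourable figure.
2. **Keep 30 patients and adjust for baseline.** Make the primary quality-of-life comparison an analysis adjusted for baseline QLQ-C30, which Table 2 already schedules at the initial visit. State its power with the assumed correlation shown: about 81% at 0.3 and 88% at 0.5, provided the SDs of 5 and 6 are those of follow-up scores. The text should say which kind of score they refer to. The cost is one sentence and a prespecified model.

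The planned reassessment after phase I is a convenient point to make the change.

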### Objectives {7}

The main goal of phase I is to assess the safety, toxicity, and maximum tolerated dose (MTD) of the Esperanza extract in patients diagnosed with metastatic gastric tumors and acute leukemias. In phase II, the focus shifts to evaluating the safety of the extract and examining its impact on improving patients' quality of life using the QLQ-C30 scale for gastric tumors. Additionally, in the context of acute leukemias during phase II, the emphasis remains on determining the safety of the extract and investigating its potential to enhance the rate of remission during induction therapy and/or facilitate hematological recovery.

In addition to the primary objectives, there are important secondary objectives for gastric tumors. One of these is to evaluate the influence of the Esperanza extract on progression-free survival and clinical response, which will be assessed using the RECIST 1.1 criteria. For acute leukemias, the assessment will focus on event-free survival, defined as the duration from enrolment to disease progression, including local or distant recurrence, second primary malignancy, primary malignancy-related death, or death from any cause, whichever comes first. Furthermore, a thorough evaluation of the impact on patients' quality of life will also be conducted.

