**Efficacy Assessment**					
RECIST		X			X
Tumor Antigens		X			X
CA199		X			X
ACE		X			X
Metabolome		X		X	X
Microbiome Analysis		X			X
Proinflammatory Cytokines		X		X	X
Circulating DNA		X		X	X
Ketone Bodies		X		X	X
Tumor Infiltration		X			X
QLQ C-30 Quality of Life Surveys		X	X	X	X
Progression-Free Survival		X			X

For newly diagnosed acute leukemias, a total of 28 new patients will be recruited, and an additional six patients will be recruited for the relapsed leukemias group. Both groups will receive continuous treatment with the Esperanza extract at the determined MTD for four weeks. Standard chemotherapy treatment for their underlying disease will be administered to both groups. At the end of the treatment cycle, safety and efficacy evaluations will be conducted. Table 3 provides a comprehensive list of the activities to be carried out during the patients' intervention.

**Table 3 Tab3:** Activity schedule for phase II clinical trial in acute leukemias

Schedule of activities				

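### The leukaemia sample size rests on an ANOVA effect size, so its 80% power is not shown for remission rate; separately, the haematologic total of 46 does not match its stated parts

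*Protocol article*

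**What the plan says.** Under Sample size {14}, the article says that for haematologic tumours "the sample size calculation was based on response criteria such as improvement, remission rate, and hematologic recovery". It then gives the method and inputs, "The ANOVA test was used, an alpha error of 0.05, a beta error of 0.20, and an effect size of 0.4", and arrives at 28. It does not say on which scale 0.4 is measured, whether 28 is a total or a group size, or what remission rate is expected with or without the extract.

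Under Objectives {7}, the phase II leukaemia efficacy question is whether the extract can "enhance the rate of remission during induction therapy and/or facilitate hematological recovery". Under Sequence generation {16a}, there is no randomisation for leukaemia; instead "the comparison of outcomes will be conducted against a historical group using propensity score matching". The number of historical controls and the matching ratio are not stated.

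On recruitment, the phase II treatment text says that for newly diagnosed leukaemia "a total of 28 new patients will be recruited, and an additional six patients will be recruited for the relapsed leukemias group". Phase I has 6 patients. Sample size {14} closes with the overall totals: "The recalculated sample size for phase I/II is 36 for gastrointestinal tumors and 46 for hematologic tumors".

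**The concern.** A sample size statement should tell the reader which difference, in which outcome, the trial can detect. Here the outcomes named include a remission rate, while the calculation uses an effect size for differences between means. The two can be linked only through a control rate, and none is given. A reader would naturally take the leukaemia part to have 80% power for remission. If that is not so for gains of moderate size, a result showing no difference could be misread as evidence of no effect.

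The second matter is one of consistency. The haematologic total is the enrolment figure for that part of the trial, and it cannot be built from the numbers the article gives.

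**Working it through.** **Inputs from the article.** Alpha 0.05; power 0.80 (beta 0.20); effect size 0.4; phase II leukaemia size 28; 28 newly diagnosed and 6 relapsed recruits; 6 patients in phase I; totals 36 and 46. Because ANOVA is named, 0.4 is taken as Cohen's f.

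**Inputs assumed.** Control remission rates of 40%, 50%, 60% and 70%; two-sided testing; one matched control per treated patient; the two groups treated as independent samples.

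**Step 1: reproduce 28.** For a one-way ANOVA, power comes from the noncentral F distribution with noncentrality f² × N, where N counts all groups. With two groups, f = d/2, so f = 0.4 is a standardised mean difference d of 0.8.

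- 26 per group: 0.4² × 52 = 8.32, critical F(1, 50) = 4.03, power 0.807. This is the smallest equal group size reaching 0.80.
- 28 per group: 0.4² × 56 = 8.96, critical F(1, 54) = 4.02, power 0.836.

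Read as 28 treated and 28 controls, the stated 28 is therefore reproduced to within two patients, with 84% power for d = 0.8.

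**Step 2: put 28 versus 28 on the remission scale.** For control rate p₀, treated rate p₁, their mean p̄ and n per group:

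power = Φ{ [ (p₁ − p₀) − 1.96 × √(2p̄(1 − p̄)/n) ] / √( [p₀(1 − p₀) + p₁(1 − p₁)]/n ) }

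Example, 60% versus 80%: p̄ = 0.70; null standard error √(2 × 0.21/28) = 0.1225; alternative standard error √((0.24 + 0.16)/28) = 0.1195. Then (0.20 − 1.96 × 0.1225)/0.1195 = −0.335, and Φ(−0.335) = 0.37.

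| Assumed control rate | Treated rate for 80% power, 28 v 28 | Gain (points) | Power for a 20-point gain | Needed per group for a 20-point gain |
|---|---|---|---|---|
| 40% | 76.2% | 36.2 | 32% | 97 |
| 50% | 84.5% | 34.5 | 33% | 93 |
| 60% | 91.5% | 31.5 | 37% | 82 |
| 70% | 97.2% | 27.2 | 46% | 62 |

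With three controls per patient (28 versus 84), power for a 20-point gain rises only to about 45% to 58%. If 0.4 had been meant as Cohen's h, the effect size for two proportions, about 98 per group would be needed: 2 × ((1.96 + 0.84)/0.4)².

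**Step 3: precision.** For a true 60% versus 80% with 28 per group, the half-width of the 95% interval for the risk difference is 1.96 × 0.1195 = 0.234. The interval would be about the observed difference ± 23 points.

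**Step 4: the totals.**

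- Gastrointestinal: 6 + 30 = 36, as stated.
- Haematologic: 6 + 28 + 6 = 40; stated 46; difference 6. Leaving out the relapsed group gives 6 + 28 = 34.

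The gastrointestinal sum shows that the 6 in phase I is meant per tumour type. If it were shared between the two types, the haematologic sum would be smaller still.

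**The case against.** Four points can be made for the plan.

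First, 28 is a workable ANOVA number. This stands. A reader might take 28 as the total across both groups, which would give only 53% power at f = 0.4, and conclude that the arithmetic is wrong. The article does not support that: all 28 are newly recruited patients who receive the extract, and the comparators come from hospital records. Nor is the per-group reading the only route to 28, since a repeated-measures ANOVA (two groups, two measurements, zero correlation) also reaches it, though the article states no such assumptions.

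Second, haematological recovery need not be a proportion. It could be measured in days, where an ANOVA might fit. This also stands, so the mismatch is established for remission rate only. The article, however, defines no continuous recovery variable and gives no standard deviation for one.

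Third, the efficacy aim is exploratory: the Discussion leaves evaluation of efficacy to phase III, and sizes are to be reassessed after phase I. This lowers the stakes but does not make the printed power statement describe remission. It does weaken two further criticisms. A reader might infer an inflated type I error from the and/or objective, but no either-or success rule is stated. A reader might also object that the statistical methods name no test for a proportion, but those tests are offered as possibilities for quantitative variables, and a condensed article may leave the rest to the full protocol or analysis plan.

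Fourth, 46 may be right and a component missing. Six further patients would close the gap. That is possible, but none are mentioned, so the article does not show which figure is wrong.

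**Conclusion.** Both points hold, and they are independent of each other.

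The 80% power is not shown for the planned remission comparison. With 28 treated and 28 matched controls, 80% power requires a gain of about 27 to 36 points, and a 20-point gain has about 32% to 46% power. These figures rest on assumed control rates of 40% to 70%, two-sided testing at 0.05, 1:1 matching and an independent-samples approximation. They take no account of any within-pair correlation or of uncertainty from the matching itself. The number 28 is not shown to be miscalculated.

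The haematologic total of 46 exceeds the sum of its stated parts by 6. It would be tempting to count this as a further reason to doubt the power, but the total plays no part in the calculation of 28. Nor can it be said that the enrolment target itself is wrong, only that the total and its components disagree.

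**What to change.** **Sample size statement.** Keep 28. State that it is the treated, newly diagnosed group, and give the number of matched historical controls. Replace the ANOVA power statement with the detectable difference in remission rate and the expected confidence interval width, over control rates that the sponsor states (ideally those of the hospital's own cohort). Report the matched risk difference in remission with its confidence interval, labelled exploratory.

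**Total.** Reconcile 46 with its components, either by correcting it or by stating who the additional six patients are.

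**Cost.** Changes of wording, plus retrieval of the historical remission rate and a count of usable controls. No extra patients are needed. The price is that the stated sensitivity for remission will look less favourable than 80% power suggests.
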